### Recruitment, randomization, and baseline interviews

We expect to recruit approximately 33 participants per month, although recruitment over the first three or four months may be somewhat lower given the time that it will take to establish a smooth and efficient process for recruitment and intervention within the jails. Recruitment should take about 24 months. Based on previous studies of brief intervention or SBIRT that reported refusal rates, we estimate that about 25% of inmates approached will refuse to participate.

Each week, Los Angeles County Sheriff’s Department staff will provide ISAP research staff with a list of names, identification numbers, and scheduled release dates for inmates who are eligible for study participation for that week. On designated recruitment days, research staff will request to see inmates prioritized by release date. Custody staff will call up inmates and escort them to the recruitment location within the jail.

The interviewer will explain the nature of the study and review the informed consent form with the potential participants. If the person agrees to participate, the researcher will obtain the required signatures on the consent form and provide a copy to the participant. Using a set of randomly ordered opaque envelopes prepared by ISAP’s Data Management Center, the interviewer will randomly assign the participant to the SBIRT group or the comparison group and will inform him or her of the assignment. For inmates who refuse to participate in the study, the interviewer will record the reason(s) provided, if any, and basic gender, age, and race/ethnicity based on visual cues.

If the participant is randomized to the SBIRT group, the interviewer will administer the baseline interview, obtain locator information for the follow-up interview, and then direct the person to the health educator, who will administer the ASSIST; the participant will then receive the appropriate intervention based on ASSIST score.

If the participant is randomized to the control group, the interviewer will administer the baseline interview and locator form and then administer the ASSIST. Having the interviewer administer the ASSIST to the control participants accomplishes two purposes: first, it ensures that we have comparable data on risk levels for participants in both study groups, and second, it ensures that the control participants receive the ASSIST in a research context rather than in a clinical context, thus strengthening the clinical contrast between the two groups. (As discussed later, there may still be a research effect on outcomes; however, this is unavoidable if we wish to collect self-report baseline data that cannot be obtained from records.) Following the interview, the interviewer will inform control participants of their risk level based on the ASSIST and will provide them with literature on reducing drug and alcohol use and HIV risk behaviors and a list of treatment programs in Los Angeles County. Control participants will not receive a brief intervention or a referral to treatment, but they may, of course, decide to enroll in treatment or seek other help on their own, which will be determined in the follow-up interview or through records.

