## Methods/design

### Setting and participants

Screening and brief intervention will occur in two jails in Los Angeles County. Men’s Central Jail houses approximately 5000 male inmates from throughout Los Angeles County. The Twin Towers Detention Facility houses about 400 female inmates from throughout the county. The majority of inmates at both facilities have been sentenced on misdemeanor charges. As noted above, brief treatment will be conducted by trained counselors from HHC-LA, either in person at the HHC-LA treatment program or by telephone. Participants needing longer term treatment will be referred to one of the county’s Community Assessment Services Centers.

Since SBIRT is intended to be a universal intervention within a target setting, all adult (18+) male and female inmates who are within two weeks of scheduled release and who are available during the times that recruitment is conducted will be eligible to participate, with the following exceptions: those who 1) lack fluency in English or Spanish, 2) are unwilling to provide locator information for follow-up, 3) plan to leave the Los Angeles area within 12 months, 4) already have a referral to treatment following release from jail, or 5) are unable to provide informed consent owing to cognitive impairment.

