### Tracking and locating for 12-month follow-up interviews

At baseline, the interviewer will ask participants to fill out a Locator Form. This form contains information that is useful for locating participants for follow-up interviews (e.g., driver’s license; names, addresses, and phone numbers of immediate relatives and unrelated friends; areas of town frequented; locations where social services are received; and probation or parole officer contacts). Other tracking resources include local and state correctional agencies that maintain publicly available websites that can be searched to determine whether a subject is in jail or prison or is on probation or parole. We will use a program developed in FileMakerPro^®^ for previous ISAP studies to record information needed for the tracking and locating process (e.g., locator data, agency contacts, letters, telephone calls, appointments). Tracking and locating procedures are described in a manual that was developed at ISAP [42] and is widely distributed by NIDA and CSAT. These procedures have been used by ISAP researchers in many studies to track and locate subjects for as long as 10 years between interview points, with follow-up rates typically at 85% or more [43]. Follow-up interviews have been conducted with subjects who are homeless, who are in jail or prison, who have absconded from probation or parole supervision, or who reside in other states or countries. In short, we expect that the detailed locator information from participants and the successful strategies used in previous studies will enable us to locate 90% of the baseline sample and, allowing for refusals and deaths, to interview at least 85% of the sample at the 12-month follow-up. We will obtain criminal justice and treatment records covering the 12-month follow-up period on all participants.

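### Locator information is collected after the arm is announced, so knowledge of the allocation can affect who is traceable for the 12-month primary outcomes

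*Protocol article*

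**What the plan says.** Under Setting and participants, the second exclusion covers inmates who "are unwilling to provide locator information for follow-up".

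The section Recruitment, randomization, and baseline interviews sets out the order of events:

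1. Sheriff's Department staff supply "a list of names, identification numbers, and scheduled release dates for inmates who are eligible for study participation for that week".
2. The study is explained and the consent form reviewed. "If the person agrees to participate, the researcher will obtain the required signatures on the consent form".
3. Using opaque envelopes, "the interviewer will randomly assign the participant to the SBIRT group or the comparison group and will inform him or her of the assignment".
4. Under allocation to SBIRT, "the interviewer will administer the baseline interview, obtain locator information for the follow-up interview, and then direct the person to the health educator".
5. In the control group, "the interviewer will administer the baseline interview and locator form and then administer the ASSIST".

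The section Tracking and locating for 12-month follow-up interviews agrees on timing: "At baseline, the interviewer will ask participants to fill out a Locator Form". The same section rests the expectation of locating 90% and interviewing at least 85% of the sample on this information, together with tracing strategies from previous studies. The Analysis plan bases both primary outcomes, drug use and alcohol use, on self-report and biological testing. The follow-up data for both are collected at the 12-month interview.

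**The concern.** Information that bears on eligibility and determines whether a participant can be found should be collected before anyone in the room knows the arm. Here both participant and interviewer know it, and the interviewer who opens the envelope also takes the locator details.

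The documents give a reason why the arms might respond differently. SBIRT participants are offered brief treatment at no cost, in person or by telephone. Where a high-risk client prefers it, contact details go to the counselor who arranges the appointment, so being reachable has a practical benefit. Control participants receive neither a brief intervention nor a referral, so being reachable brings them only the follow-up interview and its payment.

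At stake is differential loss to the one interview that yields the primary outcomes. If those lost differ from those kept in drug or alcohol use, the comparison is biased. The direction cannot be predicted: losing heavier users from the control arm would make SBIRT look worse, and losing lighter users would make it look better.

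**Working it through.** The point concerns the order of procedures, and the protocol states no figure for it, so there is none to reproduce.

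**Order of steps.** The sequence in both arms is Sheriff's list, explanation and consent, envelope, announcement of the arm, baseline interview, locator form. The tracking section places the form at baseline and describes no earlier request. The Sheriff's list is described as carrying names, identification numbers and release dates, and nothing indicates that it covers willingness to give locator information. Hence the text describes the information itself as first requested after the arm is known.

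**Inputs from the protocol.** Total sample 800, so 400 per arm; planned effect 0.20 SD; attrition allowance 15%.

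**Assumed inputs.** The documents give no rate of locator refusal. Let *g* be the extra share of one arm lost because of the post-allocation step, and *D* the outcome difference, in SD, between those lost and those kept, taken as the same in both arms.

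**Formula.** Losing a share *f* of an arm shifts the mean of those kept by *f* × *D*, so the bias in the difference between arms is *g* × *D*.

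| *g* | *D* = 0.5 SD | Share of 0.20 | *D* = 1.0 SD | Share of 0.20 |
|---|---|---|---|---|
| 0.02 | 0.010 | 5% | 0.020 | 10% |
| 0.05 | 0.025 | 12.5% | 0.050 | 25% |
| 0.10 | 0.050 | 25% | 0.100 | 50% |

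In head counts, refusal or unusable details in 1% to 5% of 800 would be 8 to 40 people. An assumed split of 2% in SBIRT and 6% in control would be 400 × 0.02 = 8 against 400 × 0.06 = 24. With *D* = 0.5 the bias is 0.04 × 0.5 = 0.020 SD, or 10% of the planned effect. This split has no source in the documents.

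The formula describes an unadjusted comparison of those observed. It overstates the problem to the extent that people with poor locator data are found by other means, or that baseline data explain the loss.

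**Power.** With a simple two-mean formula, 400 × 0.85 = 340 per arm gives 74.1%. Losing a further 10% of one arm (340 × 0.90 = 306) gives 71.8%. These values serve only to show the change; they do not reproduce the protocol's repeated-measures calculation. The issue is bias, not sample size.

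**The case against.** The exclusion concerns willingness, which can be asked when the study is explained or in the consent form, and that form is not shown. A condensed article need not describe each screening step. A reader might infer that the criterion is applied only after the envelope is opened, but that would be an inference from silence. This part of the objection stands.

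A reader might also infer that staff would have to drop a randomised person who declines the form, in breach of intent-to-treat. The document does not support that. Hypothesis testing commits to intent-to-treat, Randomization violations repeats it even for crossovers, and nothing permits removal after randomisation. The text points to retention, so no contradiction is shown.

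The safeguards also count. Staff already hold names and identification numbers, and correctional websites can be searched. Interview payments are the same in both arms. Arrest, incarceration and publicly funded treatment records are to be obtained on all participants. The baseline interview comes before the locator form, so some baseline data will exist for a person who declines. An attrition check and maximum likelihood or multiple imputation are planned.

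These points narrow the concern but do not close it. Someone willing in principle at consent can still decline, or give little detail, after hearing the arm. Administrative records do not supply drug or alcohol use. The attrition check, as described, compares completers with non-completers and not by arm. Likelihood or imputation methods do not reliably repair loss that depends on a reaction to the allocation and on unobserved use.

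**Conclusion.** The concern holds in a limited form. The stated sequence lets knowledge of the arm, on both sides of the interview, affect locator refusal and quality, and through them the ascertainment of both primary outcomes. This follows from the text in both arms.

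Its size cannot be estimated from the documents. An imbalance of 2 to 5 percentage points with a 0.5 SD difference gives a modest bias of 0.010 to 0.025 SD; larger values need a 10-point gap or a difference near 1 SD. Nothing in the documents shows that refusal would differ by arm, so to conclude that the randomised comparison is lost would go too far. This is a cheap improvement to a procedure that leaves an avoidable opening for bias in a trial planned around a small effect.

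**What to change.** In Recruitment, randomization, and baseline interviews, change the order for both arms: after consent, complete the Locator Form and confirm eligibility against all exclusions, and only then open the envelope. Anyone who declines the form is recorded as not eligible and is not randomised. Add one sentence saying that everyone randomised stays in the intent-to-treat set and that nobody is excluded under the locator criterion after allocation.

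The same interviewer completes the same form in the same session. The cost is a few minutes of interviewer time spent on people who are then not randomised.

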### Data sources

Research staff will be bilingual in English and Spanish, and consent forms, instruments, and other materials will be available in English and Spanish.

#### Baseline interview

Given the setting, the nature of the intervention, and the need to encourage participation, the baseline interview will be kept as brief as possible (about 30 minutes, rather than the hour or more that baseline interviews usually take). The domains covered will include demographics, drug and alcohol use, treatment history, stage of change and readiness for treatment, HIV risk behaviors, and crime and criminal justice history. Drug and alcohol history will be available from the ASSIST and other standard drug-use assessments. Other items will be drawn from the Intake Instrument of the Criminal Justice Drug Abuse Treatment Studies Cooperative (funded by the National Institute on Drug Abuse [NIDA]); the University of Rhode Island Change Assessment Scale (URICA [35]); and the HIV risk-behavior questions used in the NIDA Clinical Trials Network.

#### Follow-up interview

The 12-month follow-up interview will last about one hour and will include questions and scales that measure outcomes, namely, drug and alcohol use (using the ASSIST), participation in treatment, quality of life, HIV risk behaviors, crimes committed, and criminal justice contacts. Quality of life will be measured with the WHO Quality of Life–Bref Survey [36]. All participants (SBIRT and control) who report having received treatment since baseline will also be asked about their satisfaction with the treatment they received (Client Satisfaction Questionnaire-8 [37]).

#### Biological measures for drug and alcohol use

At the follow-up interview, participants will be requested to provide two oral fluids samples, one of which will be analyzed for drugs, the other for alcohol, both using onsite test kits [38,39]. Compared with urine testing, oral fluid testing is less intrusive, is more convenient, is more easily observed, makes adulteration more difficult, and provides results that have sufficient sensitivity and specificity for research purposes. The drug test will provide results for opiates, cocaine, methamphetamine, amphetamine, marijuana, and phencyclidine—the drugs most commonly used in southern California. At the direction of our Institutional Review Board, we will not collect oral fluids at follow-up interviews conducted with incarcerated subjects. In addition, oral fluids samples will not be collected from participants who are interviewed by telephone.

#### Administrative records

We will obtain records-based data on arrests and incarceration over the follow-up period from the Los Angeles Sheriff’s Department and the California Department of Justice and on participation in publicly funded treatment from the Substance Abuse Prevention and Control office of the Los Angeles County Department of Public Health.

#### Cost data

Data on the costs of the SBIRT intervention will be collected using the Brief Drug Abuse Treatment Cost Analysis Program (http://www.datcap.com[40]), which has been used to conduct cost analyses of a variety of drug abuse treatment programs, including brief intervention [41]. Costs will be collected in Year 3 and will include staff training and monitoring; staff time for screening, brief intervention, and BT; time spent by sheriff’s department employees; equipment and supplies; and other costs associated with the intervention. Given the lack of research on the use of SBIRT with offenders, it is premature to conduct a full cost-effectiveness or benefit-cost analysis. However, the cost analysis will provide policy-relevant information with regard to the cost of providing SBIRT to a jail population. Should the intervention prove to be effective in this study, the cost data will lay the foundation for a proposal to conduct a comprehensive benefit-cost analysis of SBIRT with offenders.

### Interview training and procedures

Prior to training, interviewers will need to receive clearance to work in the jails. The ISAP Training Unit and project research staff will provide a five-day training that consists of the regular ISAP training modules required of all interviewers: Good Research Practices, Safety Concerns in Dealing with Patients, and Data Collection Procedures. The training will also cover 1) familiarization with study aims, instruments, and interview procedures specific to the study; 2) confidentiality and informed consent, data integrity, and data security; 3) issues and cautions in working with offenders; 4) observation of mock interviews conducted by the project director; and 5) practice interviews with the project director. Interviewers will also receive “red flag” training on how to recognize and respond to danger to self and others, child abuse, elder/dependent adult abuse, and domestic violence. Interviewers will receive annual refresher training on these topics.

The baseline interviews will be conducted in a private office at the jail. The follow-up interviews will occur at locations that are safe, ensure privacy, and minimize travel costs. Follow-up interviews may be conducted in jails or prisons. If a face-to-face interview is not possible (e.g., the participant is located out of state), the interview will be conducted by telephone. When setting up the follow-up interview, and again at the interview, the interviewer will confirm the identity of the participant by asking for full name and birth date. As a quality check, the project director will call a 10% random sample of participants for whom follow-up interview forms are on file to verify that the interview took place. Weekly project meetings with research staff will enable problems in recruitment and data collection to be quickly identified and addressed. Several procedures will help standardize data collection and encourage accuracy and honesty in reporting, as follows: 1) trained interviewers will conduct the interviews; 2) a private interview setting will minimize distractions and ensure confidentiality; 3) interviewers will remind participants of the confidentially of the information that they provide; 4) interviewers will be attentive to signs of fatigue and offer breaks if necessary; and 5) interviewers will be trained to look for reporting inconsistencies and socially desirable versus honest responses.

Participants will be paid $20 for the baseline interview, $50 for the follow-up interview, and $10 for two voluntary oral fluids samples (one for drugs, the other for alcohol) at follow-up. For interviews in the community, payment will be in the form of a gift card provided immediately following the interview (or mailed if a telephone interview). For interviews conducted in jail or prison, payment will be in the form of either money order or cash (depending on institution procedures) deposited to the inmate’s trust account.

### Tracking and locating for 12-month follow-up interviews

At baseline, the interviewer will ask participants to fill out a Locator Form. This form contains information that is useful for locating participants for follow-up interviews (e.g., driver’s license; names, addresses, and phone numbers of immediate relatives and unrelated friends; areas of town frequented; locations where social services are received; and probation or parole officer contacts). Other tracking resources include local and state correctional agencies that maintain publicly available websites that can be searched to determine whether a subject is in jail or prison or is on probation or parole. We will use a program developed in FileMakerPro^®^ for previous ISAP studies to record information needed for the tracking and locating process (e.g., locator data, agency contacts, letters, telephone calls, appointments). Tracking and locating procedures are described in a manual that was developed at ISAP [42] and is widely distributed by NIDA and CSAT. These procedures have been used by ISAP researchers in many studies to track and locate subjects for as long as 10 years between interview points, with follow-up rates typically at 85% or more [43]. Follow-up interviews have been conducted with subjects who are homeless, who are in jail or prison, who have absconded from probation or parole supervision, or who reside in other states or countries. In short, we expect that the detailed locator information from participants and the successful strategies used in previous studies will enable us to locate 90% of the baseline sample and, allowing for refusals and deaths, to interview at least 85% of the sample at the 12-month follow-up. We will obtain criminal justice and treatment records covering the 12-month follow-up period on all participants.

### Analysis plan

#### Variables

The independent variable for analysis is treatment status (i.e., assignment to either the SBIRT group or the comparison group). With respect to dependent variables, in accordance with Consolidated Standards of Reporting Trials (CONSORT) recommendations for randomized trials [44], we divided the dependent variables (outcomes) into primary and secondary. The power analysis is based on detecting effects for the primary outcomes. The two primary outcomes are reductions in the use of drugs and of alcohol (based on self-report and biological testing). The secondary outcomes are participation in treatment (based on self-report and records) and in self-help groups (based on self-report); rearrest and incarceration (based on records); quality of life (based on self-report); and HIV risk behaviors (based on self-report).

